#### Intervention device

The device will be a 3D-printed customised oronasal mask designed to be used with PAP therapy. The mask will be created using a 3D scanner, which captures a digital impression of the patient’s face; CAD will be used to create a mould, which will then be 3D printed, with the mould then used to make the mask. The part of the mask in contact with the participants’ skin will be silicon-based.

#### Comparator device

Conventional PAP masks will be used in the usual care group. An expert clinician will make a clinical assessment of the fit and decide on the conventional mask. They will all be full face masks. Depending on procurement and supply chain, a range of full-face masks will be utilised.

The PAP devices used will be CE/UKCA marked devices. A range of devices will be used depending on procurement and supply chain. Where feasible, the same manufacturer will be used throughout the study to ensure consistency in the data collected from the PAP devices.

The devices used in the manufacturing process will include the 3D scanner, Revopoint POP 2 (Revopoint, Hong Kong). A range of 3D printers will be used to ensure the sustainability of the research. This includes stereolithography printers (Form 3, FormLabs, Germany), selective laser sintering printers (Lisa Pro, Sinterit, Poland and Fuse 30+, FormLabs, Germany) and Polyjet printers (Object 260, Stratasys).

#### Intervention

Table 1 displays the schedule of assessment and interventions by visit. Participant randomisation will be undertaken centrally by the coordinating trial team site using Sealed Envelope: https://www.sealedenvelope.com

**Table 1 T1:** Schedule of assessments and interventions by visit

Visit number	Conventional (control) mask group	Customised (intervention) mask group
1	Informed consent Facial scanning Physical assessment, including the presence of dermatitis, pressure ulcers, and eye symptoms. Vital measurements: SpO_2,_ weight, height, BMI. Demographics, Waterlow score, Co-morbidities, Rockwood frailty score Questionnaires: ESS, SWIFT and S3NIV PAP therapy device issued with conventional mask	Informed consent Facial scanning for production of customised 3D printed mask Physical assessment, including the presence of dermatitis, pressure ulcers and eye symptoms. Vital measurements: SpO_2,_ weight, height, BMI. Demographics, Waterlow score, Co-morbidities, Rockwood frailty score Questionnaires: ESS, SWIFT and S3NIV
1a		PAP therapy device issued with a customised mask
2	*Three months after the first visit* Physical assessment as per visit 1 Download data from the PAP machine *Questionnaires as per visit 1 plus interface questionnaire* *2-night cardiorespiratory sleep study* Adverse events review	*Three months after visit 1a* *Physical assessment as per visit 1* *Download data from the PAP machine* *Questionnaires as per visit 1 plus interface questionnaire* *2-night cardiorespiratory sleep study* *Adverse events review*
3	*Six months after visit 1* Physical assessment as per visit 1 Download data from the PAP machine *Questionnaires as per visit 2* *2-night cardiorespiratory sleep study* Adverse events review	*Six months after visit 1a* Physical assessment as per visit 1 Download data from the PAP machine *Questionnaires as per visit 2* *2-night cardiorespiratory sleep study* Adverse events review Issue conventional mask for ongoing treatment

BMIbody mass indexESSEpworth Sleepiness ScorePAPpositive airway pressureS3NIVS3 Non-Invasive VentilationSWIFTSleepiness-Wakefulness Inability and Fatigue Test

A 3D scan using a hand-held scanner of all participants’ faces will be collected for participants in both groups.

Those in the control arm will be fitted with a conventional PAP therapy mask and undergo an initial 10 min trial of PAP therapy to assess for mask leak, skin reactions and comfort scores. Once an acceptable mask is fitted, patients will go on to have PAP therapy as per their regular PAP regime. An additional visit (visit 1a) will be required for those in the intervention arm once their customised mask has been manufactured. Participants will undergo an initial 10 min trial of PAP therapy with the customised mask to assess for mask leak, skin reactions and comfort scores. If there are no serious adverse events (SAEs)/reactions during the PAP trial with the 3D-printed mask, patients will go on to have PAP therapy as per their normal PAP regime.

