### Data management

#### Sample size

A sample size of 160, with 80 per group, is required for a power of 80%, with a significance of 5%, assuming an effect size of 0.50 and allowing for a 20% dropout rate. The effect size was determined using data from previously published research^14^ compared with a cohort of randomly selected patients under the care of RFL. This method ensured that the power calculation was relevant to a United Kingdom (UK) population.

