#### Analysis

Descriptive statistics will be used to report patient demographics. The hypothesis will be tested by comparing the difference between the groups in residual AHI (the primary outcome) at the primary endpoint (6 months) using linear regression adjusting for score at baseline and stratification variables (age as a binary variable and ethnicity) on an intention-to-treat basis. Residual AHI has been chosen as the primary outcome measure as, where interface fit is poor, residual AHI has been shown to be high. Furthermore, it is a measure of treatment effectiveness, which can be used for both CPAP and NIV. The pros and cons of each potential primary outcome measure were discussed with PPI workshop attendees who agreed AHI was a suitable and acceptable primary outcome. AHI will be measured for two nights via a home-based cardiorespiratory sleep study, and the worst (higher AHI) of the two nights will be used. The analyses will be repeated using the 3-month results as a secondary outcome measure.

For secondary outcome measures, differences between groups will be compared using linear regression adjusting for respective scores at baseline and stratification variables. The analyses will be repeated using the results at 3 months.

The interface questionnaire will be analysed using descriptive statistics, bivariate analysis and ordinal regression. Dropout rates between groups will be compared using a χ^2^ test. The analyses will be repeated using the results at 3 months.

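### Customised-arm visits are dated only from mask issue, so a randomised participant who never receives the mask has no scheduled 3- or 6-month sleep study, despite the intention-to-treat analysis

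*Protocol article*

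**What the plan says.** Table 1 (Intervention section) issues the device and conventional mask to controls at visit 1 and dates their visits 2 and 3 at three and six months from that visit. In the customised arm, device and mask are issued at visit 1a, and visits 2 and 3 follow at three and six months from there; the last is set at "Six months after visit 1a". The text adds: "An additional visit (visit 1a) will be required for those in the intervention arm once their customised mask has been manufactured". No maximum wait is given.

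Both arms have a 10-minute trial of therapy. Customised-arm participants continue "If there are no serious adverse events (SAEs)/reactions during the PAP trial with the 3D-printed mask"; nothing is said about those who do react. For controls the condition is "Once an acceptable mask is fitted, patients will go on to have PAP therapy as per their regular PAP regime", and their visits stay dated from visit 1.

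The Analysis section compares residual AHI at 6 months on an intention-to-treat basis. It also states "Dropout rates between groups will be compared using a" chi-squared test, without giving a starting point or window. The Withdrawal and stopping criteria section covers only voluntary withdrawal and the retention of data already collected.

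**The concern.** An intention-to-treat comparison needs an outcome time for everyone randomised. Here the outcome time in one arm depends on an event after randomisation: the mask has to be made and issued. If that does not happen, the schedule generates no 3-month or 6-month sleep study, and no analysis plan written later can recover a study that was never done.

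The people at risk of being missed are not a random subset. They drop out of the schedule because of steps belonging to the intervention, such as manufacture or a reaction at the mask trial. Leaving them out would tend to remove failures of the customised mask from its own arm, with no matching removal among controls.

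**Working it through.** **Time origin, arm by arm**

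| | Control | Customised |
|---|---|---|
| Device and mask issued | Visit 1 | Visit 1a, after manufacture |
| 3-month sleep study | 3 months from visit 1 | 3 months from visit 1a |
| 6-month sleep study | 6 months from visit 1 | 6 months from visit 1a |
| Date if the mask is never issued | Still runs from visit 1 | None stated |
| Follow-up if the 10-minute trial fails | Still dated from visit 1 | Not stated |

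The moment of randomisation is not stated. It must precede visit 1a, because only one arm has that visit and controls receive their mask at visit 1.

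**The plan's sample size reproduces.** The Sample size section gives 80 per arm, "assuming an effect size of 0.50 and allowing for a 20% dropout rate". A two-sided 5% t-test with 80% power needs 63.77, so 64 per arm; 64 / (1 − 0.20) = 80 per arm, 160 in total. The time-origin problem does not alter this figure.

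**Effect on power if non-starters are lost.** Let f be the assumed share of the customised arm without an endpoint, on top of the planned 20% dropout. With 64 controls and 64 × (1 − f) customised-arm participants analysed, and d = 0.50:

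- f = 0: power 80.1%
- f = 5% (60.8 analysed): 79.1%
- f = 10% (57.6 analysed): 78.0%

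Lost power is minor; the issue is bias.

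**Bias from omission.** The customised-arm mean is understated by

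bias = f × (mean AHI of those omitted − mean AHI of those who start).

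The protocol gives neither f nor these means. Assume f = 5–10%, that is 4–8 of 80.

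| Assumed state of those omitted at 6 months | Difference in AHI | f = 5% | f = 10% |
|---|---|---|---|
| On a conventional mask, 5 events/h worse | 5 | 0.25 | 0.50 |
| Untreated, AHI 15 (the entry floor), against 7 | 8 | 0.40 | 0.80 |
| Untreated, AHI 30 (assumed), against 7 | 23 | 1.15 | 2.30 |

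The 5 is borrowed from the proposed minimally important difference in the Assessment section. The 7 is that section's good-control threshold, used as a stand-in for the mean of those who start; it is not a predicted arm mean. Against 5 events/h, the range is 0.25 / 5 = 5% to 2.3 / 5 = 46%.

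On the standardised scale, if those omitted are 0.5–1.0 SD worse, the bias at f = 10% is 0.05–0.10 SD against a design effect of 0.50 SD.

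**The case against.** The strongest reply is that the two anchors are deliberate and sensible. Both mark the same event, issue of device and mask, so both arms are assessed after three and six months on therapy. That stands, and the remedy keeps it for those who start.

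A second reply is that a journal article condenses the protocol and that follow-up of non-starters may be written elsewhere. It is true that nothing here says they are excluded. But the visit schedule is printed, and as printed it gives these participants no assessment date while the analysis is called intention-to-treat.

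Several stronger readings are tempting and are not supported:

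- **That the intention-to-treat comparison is already broken.** The article states no exclusion, and the number affected may be close to zero.
- **That anyone who fails the 10-minute trial has no dated endpoint.** Someone who attends visit 1a and reacts has a visit 1a date. The condition governs going on to therapy, not attendance at visits 2 and 3. What is missing is a statement of their follow-up.
- **That controls are refitted until a mask suits, so only the customised arm has a hurdle.** Repeat fitting is not described, and controls also have a fit condition with no stated path if it is not met. The difference is that their visits stay dated from visit 1.
- **That the dropout test compares unequal windows.** The article gives no window. Counting from device issue would give equal ones. Counting from randomisation to visit 3 would lengthen the customised arm's window by 4/26 = 15% to 8/26 = 31% under an assumed 4–8 week wait. The window is unspecified rather than shown to be unequal.

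A fallback date also does not recover people who withdraw from the study, in either arm.

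**Conclusion.** The point holds in a limited form. The schedule leaves a randomised customised-arm participant who remains in the study without a mask with no scheduled primary assessment. It also leaves the follow-up after a reaction in the 10-minute trial unstated. Both sit awkwardly with the intention-to-treat analysis, and the missing date can arise only in the customised arm.

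The likely direction favours the customised mask, provided those lost would have had a higher AHI than those who start. The size cannot be established from the protocol. The range of about 0.25–0.5 events/h (alternative conventional mask) up to about 2.3 events/h (untreated, AHI 30) rests wholly on the assumed 5–10% loss and the assumed treatment at six months. The upper figure is an extreme case, not an expectation. This is a gap to close by a short amendment, not evidence that the trial's comparison is invalid.

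**What to change.** Keep device issue as the clock for those who start. Then:

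1. Add to Table 1 that customised-arm participants without a visit 1a have visits 2 and 3 at a fixed fallback date timed from visit 1, with the sleep study done on whatever treatment they are then receiving.
2. State that all randomised participants, including those who react in the 10-minute trial, remain in follow-up and are analysed as allocated.
3. Record the randomisation date and the wait for the mask.
4. Specify that the chi-squared dropout comparison counts from randomisation over one common window in both arms, and report dropout before and after mask issue.

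The clinical path after a failed 10-minute trial is for the protocol authors to reconcile; nothing here prescribes it.

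The cost is a short amendment and a few already-planned assessments kept for non-starters. The effect estimate may be slightly diluted. If 5–10% of the arm gained no benefit at all, the effect would be 0.50 × 0.95 = 0.475 to 0.50 × 0.90 = 0.45, and power with 64 per arm (normal approximation) would fall from 80.7% to 76.6–72.1%. That is the effect an intention-to-treat analysis is meant to estimate.

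The Timelines section gives an end date of May 2025. If visits can no longer be added, items 3 and 4, analysis as allocated and a count of participants without a visit 1a can still be settled before analysis.

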### Ethics and dissemination

#### Ethics

This protocol has been reviewed by the Hampshire B Research Ethics Committee (REC reference: 22/SC/0405), who have granted a favourable ethical opinion.

#### Consent

Participants who are unable to provide informed consent are excluded from the study. The research team will obtain consent before the study baseline measurements and after the participant’s information sheet review. Potential participants will be given a minimum of 24 hours to consider if they wish to participate in the study. Consent will be obtained from participants who are non-English-speaking using a translator.

#### Confidentiality

All data will be handled in accordance with the General Data Protection Regulation V.2018. Data collected will be password protected and only accessible by the research team.

Facial scans will be transferred securely from RFL to University College London (UCL) utilising nhs.net secure email. All members of the investigatory team who will need to access the facial scans of the participants will be provided with a nhs.net email account. Facial scans will be kept securely on UCL computers, password protected, and only accessible to the investigation team. Copies of facial scans will not be stored on UCL computers after the duration of the study and will be archived in accordance with UCL policy. Participants will give consent for the transfer of the facial scans and for their facial scans to be stored on UCL and RFL computer systems during the trial. Facial scans will not be used in any publications or other dissemination without participants’ prior explicit consent. The RFL Caldecott Guardian approved this protocol.

#### Sponsor

University College London Joint Research Office will act as the sponsor.

#### Audits and inspection

Trial-related monitoring, audits, Research Ethics Committee review and regulatory inspections will be conducted in line with UK policy framework for health and social care research.^25^

#### Trial closure

The end of the trial will be on completion of 160 participants consented and completion of the primary end point.

The trial will be suspended for investigations in the following circumstances:

**•** If a SAE is noted in 20% or more of the participants

#### Trial management

A trial management group will monitor all aspects of the conduct and progress of the trial, ensure the protocol is adhered to and take appropriate action to safeguard participants in the quality of the trial. The trial steering committee (TSC) will provide overall supervision of the trial and ensure it is conducted in accordance with the principles of good clinical practice and the relevant regulations. The TSC will meet 6 monthly during the time of the trial. A Data Management and Ethics Committee will meet annually to provide oversight on the need for any interim analysis and ensure participants’ safety by reviewing recruitment, adverse events and trial completion rates.

#### Publication policy

The results of this clinical investigation will be submitted for publication as an abstract at appropriate conferences and as a journal article to appropriate journals. Authorship will be determined in concordance with the International Committee of Medical Journal Editors authorship guidelines and UCL publication policy.

#### Timelines

The trial start date was January 2023, with an end date of May 2025 and anticipated publication date of December 2025.

## Discussion

The need for research focusing on developing patient-specific interfaces for PAP therapy that are acceptable to patients and avoid side effects such as leaks, pressure ulcers and ineffective PAP therapy has been recognised as a priority.^26^ The outcomes of this study will inform the sleep and ventilation community on the prospects of customised interfaces for PAP therapy. The outcomes from this trial could inform the design and manufacturing processes of future customised PAP therapy interfaces and support future trial conduct. Secondary outcomes and the assessment and diagnostic data from this trial could prove helpful in informing the sleep and ventilation community on the ongoing care and management of patients with SDB.

There are limitations to this trial. It is only feasible to assess medium-term (6-month) outcomes within the scope of the secured funding. Furthermore, due to the scope of the funding, it is not possible to blind assessors. The interventional nature of the trial design means it is not possible to blind participants. This is a single-site study, which is a further limitation potentially reducing the generalisability of the results. It has not been possible to include a health economics assessment due to the constraints of the secured funding. PPI groups have expressed frustration at the limitation of providing customised masks within a clinical trial and that due to regulations, the customised masks cannot be utilised outside of the clinical trial. It was not feasible or necessary (as agreed by the sponsor and the research site) for this clinical trial to be registered with the Medicine and Health Care Products Regulatory Agency. Thus, the results of this research cannot be used towards regulatory approval.
